### Inclusion and exclusion criteria

We aim to be as inclusive of the community as possible and hence have minimal exclusion criteria. We will recruit adult women (18–50 years) who plan to reside in the community for at least the next 2 years. Women will be excluded if they have a serious physical or psychological condition that might affect their ability to complete outcome measures or participate fully, are pregnant or breast feeding, taking weight control medications or who have had bariatric surgery. To be inclusive of all community members, body mass index (BMI) is not used as an inclusion or exclusion criteria.

### Program theory and implementation strategy

The HeLP-her Rural intervention is based on our previous successfully delivered HeLP-her intervention [15], which was delivered to women living in urban communities. The intervention has been adapted to address potential barriers to implementation in a rural setting. Barriers for both delivery and participation in health programs in a rural setting include travel distance and time required to attend sessions. To address potential participation barriers we will substitute some face to face meetings with remote delivery, be flexible in meeting times ensuring convenience, hold sessions in local settings such as schools, pre-schools and community centres, and allow young children to attend.

The following principles will guide the implementation and evaluation of HeLP-her Rural in this community setting. These principles are based on our previous work [15], similar interventions [16] as well as national and international guidelines and frameworks [17].

The intervention will

1. Align with national and international health priorities

2. Be theory driven

3. Include multi-sectoral communication and engagement

4. Be adaptable to local context

5. Aim to recruit a representative sample of the target population

6. Address barriers to participation and be a low burden on participants to maximise reach

7. Align with and support, local programs and strategies thereby adding value to local prevention interventions

8. Provide the highest quality evidence available

9. Be pragmatic with recruitment and delivery as close to real life as practicable

10. Assess reach, effectiveness, adoption and implementation via a comprehensive community evaluation

11. Be low intensity to ensure low cost and sustainability

#### Program theory

The HeLP-her intervention is based on the self-determination theory (SDT) with motivational interviewing (MI) [18] and self-management principles providing the basis for content, resources and any personal contact by the program facilitator. In keeping with the SDT, HeLP-her aims for participants to consider their own personal needs, skills, priorities and goals. Application of MI aims to move participants to choosing and then valuing the outcomes of their behaviour. The content is non-prescriptive, instead providing general health messages and a focus on small achievable changes to enhance self-efficacy and sustainability of behaviour change. We adapted the taxonomy developed by Haase et al. to identify SDT components in the HeLP-her Rural program [19] (Table 1).

**Table 1 T1:** SDT components of HeLP-her Rural

**SDT components**	**Content activities**
**Competence**	Describe the pattern of weight gain in women
	Explore value and benefits of changing behaviour
	Introduce general health messages based on physical activity and healthy eating behaviours
	Identify personal barriers and enablers to behaviour change.
	Learn behavioural skills such as goal setting, problem solving, relapse prevention, self-monitoring
**Autonomy**	Explore beliefs and value of changing personal behaviours, identify personal priorities
	Explore small achievable steps and realistic expectations
	Explore choices and identify personal priorities, goals and action plans
	Explore where to seek further information and support
	Learn how to monitor and review progress
	Explore ambivalence and barriers
**Issues relating to people, environment and context**	Support links within the community
	Engage support from friends and family

### Program Implementation strategy

A comprehensive communication plan and engagement framework has been developed in order to ensure efficient multilevel engagement across communities (Table 2).

**Table 2 T2:** Community communication and engagement strategy

**Stakeholder group**	**Method of contact**	**Purpose**
Government Departments	Letter to provide general program information and point of contact	Government departments can be powerful allies if the program aims align with government targets. They have knowledge of communities and can connect to local stakeholders.
Local health sector and local government	Telephone call followed by email of program information and flyers.	Local health workers and local government workers have good local knowledge of their own population, health issues, local champions and potential collaborators. They can assist recruitment and reach through and their databases and contacts and support with venues.
	Regular program updates	
Private sector and	Telephone call and follow up email.	Local champions have good communication skills and support local recruitment. They distribute flyers and encourage their networks to participate.
Local champions		
Community sector, sports clubs, women’s groups, neighbourhood houses	Telephone and send program information and flyers.	Local organisations provide opportunity for recruitment, distribute flyers and identify potential links with local programs.
All local print and radio media outlets identified	A media release sent, followed up by a telephone call to the editor/producer.	We focus on local newspapers, offer photo opportunities and interviews to increase awareness and recruitment.
School Principals, Kindergarten Directors	Telephone calls, meetings, and program information.	Schools, kindergartens, childcare give direct access to participants. Principal support can validate the program. They provide practical support by distributing and promoting the program, providing space and refreshments.

#### Recruiting strategies

Simple recruiting methods will include in-person, letters and flyers, media and ‘local champions’. Based on our previous experience and the age of our target group, a primary source of recruitment will be day-care, pre-school and primary schools. The recruitment strategy in the 6 weeks prior to intervention commencement includes: 6 weeks prior communicate with primary school principles, pre-school and day care centres and engage their support; 4 weeks prior distribute letters and flyers to all families in primary schools and pre-schools; 4 weeks prior send a media release to all local media outlets; 2 weeks prior researchers visit each town to meet with local stakeholders and recruit in person. From prior experience we believe women respond better to program recruitment when there is some personal interaction. Women will be invited to express interest in person, via text message, telephone, and email or by returning a form to a collection point. Interested women will be screened by telephone and if eligible sent information packs including informed consent and baseline questionnaires prior to program commencement.

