**Methods:**

Here we describe the rationale, design and implementation of a Healthy Lifestyle Program for women living in small rural communities (HeLP-her Rural). The primary goal of HeLP-her Rural is to prevent weight gain using a low intensity, self-management intervention. Six hundred women from 42 small rural communities in Australia will be randomised as clusters (n-21 control towns and n = 21 intervention towns). A pragmatic randomised controlled trial methodology will test efficacy and a comprehensive mixed methods community evaluation and cost analysis will inform effectiveness and implementation of this novel prevention program.

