### Selecting communities

Victoria is a southern State of Australia with 34 Shires of defined geographical boundaries. Population statistics and socioeconomic data are readily available for each. Twelve of these Shires will be excluded from recruiting because of potential confounding related to their participation in a Government funded preventative health campaign. Within the remaining 22 Shires, all small rural towns with populations of between 1500–10,000 persons, located within a radius of between 100 km and 400 km from Melbourne Central Business District (CBD), will be eligible for randomisation. Town selection criteria is based on size and distance from the CBD as these factors are likely to impact on availability and access to health and community services readily available in larger regional towns. Based on these criteria, 44 towns will be eligible for randomisation.

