### Sample size calculations

In the calculation of sample sizes for the primary outcome (weight change over 12 months) adjustments will be made for the cluster design. The variance inflation factor (VIF) used to achieve this is determined from the average cluster size and the Intra-Cluster Correlation (ICC). We have powered the trial to detect a difference of 1.0 kg in weight between groups at 12 months based on our previous trial [4] and estimated population weight gain [3]. Assuming a significance level of 90% for a two-sided test, 196 women per group will be required to detect the absolute difference in weight with 80% power. The actual ICC calculated in the previous HeLP-her was −0.02 using Generalised Estimating Equations (GEE) [14], and despite the negative value is assumed to be equivalent to zero. However, we are assuming some clustering in this setting although small, and as there is little published data on which to base an estimate in rural community groups, we have assumed an ICC =0.02, cluster size m = 15, and a VIF 1.28 (1 + (m-1)*0.02)*195). Therefore, 250 women per group will be required and allowing for 20% attrition in participants over 12 months we plan to recruit 600 women in 40 clusters of 15 women. Because of the complexity and cost of the RCT we plan to oversample by 2 towns and randomise 42 towns using computer generated numbers, thereby allowing for any inadvertent recruiting issues.

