### Control group

Participants attend in groups of approximately 15 women and following completion of baseline questionnaires and measures, receive a single one hour non-interactive women’s health information session focusing on a general women’s health. Content will be based on readily available Australian Dietary Guidelines and Physical Activity Guidelines for adults [20,21] and associated pamphlets provided. No individual advice on weight will be provided or further support or contact for the duration of the 2-year program.

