### Outcome measurements

The primary outcome of HeLP-her Rural is the difference in weight gain between the control and intervention communities at 1 year and 2 years. Weight, height and waist and hip circumference measurements will be collected by trained researchers (unblinded) at baseline, 1 year and 2 years. Blinding is not generally feasible in pragmatic community wide research. Measurements will be taken in light clothing, without shoes and with an empty bladder. All participants will be weighed to the nearest 0.1 kg on calibrated electronic scales (Tanita WB110AZ). Height will be measured using portable stadiometer to the nearest 0.1 cm. Dietary intake will be assessed using the Cancer Council Australia Food Frequency Questionnaire [22] and physical activity, via the International Physical Activity Questionnaire (long version). An adapted physical activity and dietary self-management questionnaire [23] and PANSE self-efficacy endpoints via questionnaire [24] will be collected.

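### Women appear to be recruited after their town is randomised, and nothing keeps recruiters, screeners, champions or women unaware of the arm, so the arms can differ in who joins

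*Protocol article*

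**What the plan says.** **Selection and randomisation of towns.** Selecting communities defines eligible towns by shire, population and distance from the city, and ends: "Based on these criteria, 44 towns will be eligible for randomisation". Sample size calculations needs 40 clusters of 15 women but plans to "randomise 42 towns using computer generated numbers, thereby allowing for any inadvertent recruiting issues".

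**Recruitment of women.** Recruiting strategies sets a timetable: "The recruitment strategy in the 6 weeks prior to intervention commencement includes" contact with schools and day care, then letters, flyers and a media release, and finally "2 weeks prior researchers visit each town to meet with local stakeholders and recruit in person". After that, "Interested women will be screened by telephone and if eligible sent information packs including informed consent and baseline questionnaires prior to program commencement". Table 2 adds local champions, who distribute flyers and encourage their networks to take part.

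**Blinding.** The only statement is in Outcome measurements, on weight, height, waist and hip: "measurements will be collected by trained researchers (unblinded) at baseline, 1 year and 2 years". The next sentence says that blinding is generally not feasible in this type of research.

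**Order at the first session.** In the Control group, women "following completion of baseline questionnaires and measures, receive a single one hour non-interactive" information session. The week 1 description under The intervention has the same order: baseline first, content afterwards.

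**The concern.** Randomising towns makes the arms comparable only if the women who enrol do not depend on their town's arm. When women are approached, screened and consented after allocation, and people in that chain know the arm, two things can differ between arms: how hard and in what terms the program is promoted, and which women choose to come. An interactive program with a manual, a coaching call and a year of text messages may draw different women from a single talk with no further contact.

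The primary outcome is weight gain, which plausibly depends on motivation to manage weight. A difference between arms in who joins is then selection bias on the primary comparison. Adjusting for baseline variables removes only the part that those variables capture. The trial looks for a difference of 1.0 kg, so a bias of a few hundred grams would matter.

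**Working it through.** The point concerns the order of steps and who knows what. The article gives no figure to reproduce, so the sections are set side by side.

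**1. Does randomisation precede recruitment?** The article does not say so outright, but two places imply it.
- Eligibility uses only characteristics of the town. No enrolled women are needed for a town to be randomised.
- 600 / 15 = 40 towns are needed and 42 are randomised, so 42 − 40 = 2 are spare. The stated purpose is to cover recruiting problems. Spare *randomised* towns serve that purpose only if the problems appear after randomisation.

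**2. Is the arm known before baseline is complete?** Outcome measurements names baseline among the occasions at which the measuring researchers are unblinded. A list kept sealed until baseline is finished would leave them blinded at that visit. The text as written therefore has at least part of the research team aware of the arm at or before baseline.

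**3. Can people in the recruitment chain affect who joins?** Yes, by the article's own account.
- Recruiting strategies says that women respond better when there is personal interaction.
- Champions use their own networks.
- Telephone screening applies a criterion that needs judgement (Inclusion and exclusion criteria): whether a serious condition might affect a woman's ability to complete measures or participate fully.

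**4. Is there a safeguard?** None is described. Nothing says that recruiters, screeners, champions or women are unaware of the arm, or that women are identified before it is revealed.

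**5. What would a bias do? (scale only)** The bias *b* is assumed. The article gives no value and none can be derived from it.
- Inputs from Sample size calculations: 196 per group before inflation, a 1.0 kg difference, 80% power, VIF = 1 + 14 × 0.02 = 1.28, and 250 per group after inflation. The significance level is given as 90%. It is read here as α = 0.10, with α = 0.05 alongside.
- No SD is stated. From n = 2·SD²·(z₁₋α/₂ + z₀.₈₀)² / 1.0², the implied SD is √(196/2) / (1.645 + 0.842) = 3.98 kg at α = 0.10, and √(196/2) / (1.960 + 0.842) = 3.53 kg at α = 0.05.
- SE = SD·√(2 × 1.28 / 250) = 0.40 kg and 0.36 kg respectively.
- Rejection rate with no true effect = 1 − Φ(z₁₋α/₂ − b/SE) + Φ(−z₁₋α/₂ − b/SE).

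| Assumed *b* (kg) | α = 0.10 | α = 0.05 |
|---|---|---|
| 0 | 10% | 5% |
| 0.1 | 11% | 6% |
| 0.2 | 14% | 9% |
| 0.3 | 19% | 13% |
| 0.5 | 35% | 29% |

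A larger sample shrinks the SE but not *b*, so for a given bias the error rate would rise with sample size.

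**The case against.** The strongest reply is that bias depends on when the arm is disclosed, not on when the list is generated. A list drawn early and kept sealed would do no harm, and a condensed article may leave concealment to the full protocol. Recruiting strategies also sets one timetable for all towns, with no distinction by arm, and the trial commits to CONSORT. It is true that no sentence discloses the arm to recruiters. But a list sealed until baseline is complete does not fit measurers who are unblinded at baseline. The point therefore rests on something the article states, and not only on its silence. A common timetable does not conceal the arm, and a reporting guideline does not supply a concealment procedure.

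The abstract could also be cited for the opposite order: "Six hundred women from 42 small rural communities in Australia will be randomised as clusters". A reader might infer that the women are in place before randomisation. The body does not bear this out: it makes towns the randomised units and chooses them without reference to enrolled women.

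Several stronger readings are tempting and are not supported:
- **That the recruiters are stated to be unblinded.** The word is applied to those taking measurements. That recruiters know the arm is an inference.
- **That randomising first is a stated fact.** It is implied by the reason given for oversampling.
- **That towns which fail to recruit will be dropped.** The article describes a buffer and gives no rule for dropping or replacing towns.
- **That recruiters will promote the program differently by arm.** The article leaves this possible and does not plan it. In-person contact is one of several routes.

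**Conclusion.** The point holds as a weakness in how the comparison groups are formed. Towns appear to be randomised before women are recruited, the measuring researchers are unblinded from baseline, and no step keeps the arm from those who recruit, screen, promote or join. The arms can therefore differ in who joins. It should be corrected, because the fix is cheap and analysis can repair such a bias only in part.

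The conclusion rests on two readings: that the oversampling clause implies randomisation before recruitment, and that the unblinded statement covers the baseline visit, as its wording says. A reader might wish to express the bias as a share of the 1.0 kg target. The article gives no basis for that, and the true bias could be zero. The error rates tabulated above show sensitivity to assumed values and do not estimate the bias.

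**What to change.** 1. State the order of randomisation, recruitment, consent, baseline and disclosure of the arm, and who knows the arm at each step.
2. Have the allocation list held by someone outside the recruiting and screening team.
3. Use one identical, neutral recruitment text, flyer and telephone screening script in all towns, and give stakeholders and champions the same material.
4. Reveal each town's arm only after its women have consented and completed baseline questionnaires and measures. Both arms already do this before any content, so the sequence of the session need not change. Limit the unblinded statement to the 1-year and 2-year visits.
5. Report numbers approached, eligible and consenting by arm, and account for every randomised town, including the two spares.

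Cost: staff and materials for either session must be ready at each town's baseline session, including facilitators with the program-specific training, and someone must hold and release the list. This is a modest burden, though not nil. The 1-year and 2-year measurements can stay as planned.

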#### Facilitator training

Facilitators who have completed program specific training will deliver the intervention, including phone coaching. Facilitators will be required to have a tertiary qualification in health sciences and undergo one day training. Facilitators need excellent interpersonal skills, a sound knowledge of evidence based practice, an understanding of health, health behaviour, nutrition, physical activity and some knowledge and experience in communicating with a variety of sectors. Program specific training includes both theory and practical components and motivational interviewing techniques.

#### Program resources

Program resources (peer reviewed and consumer tested) include an interactive manual containing assessments, health information, personal stories, as well as tools to self-monitor and assess progress that aim to develop and improve skills in self-management. Additionally, intervention participants will have access to a password protected website containing information on the trial, health information, notification of session times and team information and contact details.

#### Program fidelity and adherence

Program fidelity will be maintained by self-assessment using a checklist completed by the facilitator following delivery and reviewed by the research assistant who attended the same session to reduce potential reporting bias. Participant adherence is checked at 12 weeks in the phone coaching session where participants will be asked if they have completed the manual activities. Participants will work through missing action plans or manual activities with facilitators to ensure the intervention is received as intended.

### The intervention

#### Intervention components and delivery overview (Figure 1)

**Figure 1 F1:**
[figure not shown]
HeLP-her Rural intervention flow chart.

Week1: Groups of approximately 15 participants will attend a single group session held at a local community centre such as a primary school, community hall, pre-school, club or health service. Following completion of baseline measures and questionnaires a trained facilitator will deliver the skill-based activities in small groups. Participants will complete section 1 during the delivery session, with activities and discussion led by the facilitator. Following the session, women will complete the manual activities in their own time over the next 2–4 weeks. Women will be given access to the program website.

Weeks 2–12: Text messages will be sent to mobile phones weekly in the first 4 weeks, then one every 4 weeks to remind participants of intervention behavioural messages and to complete manual activities.

Week 12: One 20-minute telephone coaching call, based on motivational interviewing will be delivered to all intervention participants. The telephone call will also check compliance and ensure program activities have been completed

Weeks 12–52: On-going support will be provided by monthly mobile phone text messages sent to mobile phones to remind participants of intervention behaviour messages.

